1.1. Project title

Online Intervention Study in Anxiety Disorders with Cognitive Behavioral Therapy  
and Positive Psychology.

1.3. The study presented is: a project financed by

third parties

University internal project number/cost center (if applicable):

t.n.z.

an internal university project a

dissertation (PhD thesis) a

master's thesis/diploma thesis

Name of the supervisor:

Submission was requested

By:

Supervisor

Study law body

1.4. Why is a decision of the ethics committee required (specify publication organ in case of publication)?

This is a study of an intervention with patients suffering from an anxiety disorder (generalized anxiety disorder, social anxiety disorder/social phobia and/or panic disorder with or without agoraphobia). The publication of three papers is planned (publication organ not yet known)

1.5. Has the project already gone through a review process?

Yes

No If yes, at which institution? ten enclose!

Gutach-

1.6. Are there already votes from other ethics committees?

Yes

No

If yes, attach votes!

## 2. structured summary of the project

### 2.1. Project type

This is an online intervention study in a group setting with an efficacy and a process study. Cognitive Behavioral Therapy and Positive Psychotherapy are compared.

### 2.2. Subject

Clinical psychology, psychotherapy, positive psychology

"Therapy Tool for Anxiety Disorders" by Hagena and Gebauer (2014). The treatment manual of the control group is thematically based on that of Positive Psychotherapy, but strongly shortened. The treatment manuals of PPT and KVT each comprise 12 group sessions of 90-100 minutes each and one individual session. The treatment manual of the control group comprises 12 sessions, three of which (the first, the sixth and the twelfth) take place in an online group setting, and the remaining nine are self-completed with the help of instructional videos and e-mail communication. All therapy sessions take place online. The individual groups consist of six to eight participants. The participants in each group also have access to a website created specifically for the study. This website provides work materials, audio files and instructional videos. In addition, it offers the possibility of contacting the study director via a chat function; it also serves as a virtual bulletin board to make certain exercises visible in anonymized form. The study includes three measurement time points, a pre- and post-measurement and a follow-up after three months. The treatments are carried out by psychologists in training as clinical psychologists and psychological psychotherapists in Austria and Germany. All psychologists are intensively trained in the respective manuals, participate in regular intervision sessions and receive supervision from experienced representatives of Positive Psychology and Cognitive Behavioral Therapy at regular intervals. All group sessions are recorded and discussed in the supervision. Each session is checked for adherence to the manual. As mentioned above, the study also includes a process efficacy study. In this study the intra-session processes as well as the inter-session processes of the therapy with Positive Psychotherapy and Cognitive Behavioral Therapy will be evaluated and related to the therapy outcome. Intra-session processes are understood as all those changes that occur directly in response to specific events in the therapy session, whereas inter-session processes are defined as processes of change between two sessions that are brought about by memories and representations of the session (Orlinsky & Geller, 1993). Intra-session processes will be assessed with the help of the Berner Stundenbeurteilungsbogen für Patienten (Flückiger et al., 2010), where patients will be asked after each session whether they have experienced it and whether they think it has brought progress, on the one hand in the sense of the

The intersession processes are recorded with the help of the Hartmann and Orlinsky Intersession Questionnaire. The intersession processes are recorded with the help of the Hartmann and Orlinsky intersession questionnaire. In addition to the recording of the processes, it is to be examined in particular to what extent Positive Psychotherapy and Cognitive Behavioral Therapy differ in the therapy processes (intra- and intersession processes) and which variables of both process types predict the therapy success. The control group is not included in the process study. It serves as a comparison group for the effectiveness study in order to examine the effect of a low-threshold Positive Psychology intervention compared to a guided intervention. In order to examine the effect of process variables on therapy outcome (decrease in anxiety symptomatology and general psychosocial distress, increase in happiness experience, life satisfaction and quality of life), two global indicators are formed: 1. frequency and intensity of intra- and intersession activities and 2. emotional valence of intra- and intersession processes (positive vs. negative). The aim of this study is to identify variables of change, to gain knowledge about the therapy processes and thus to optimize the therapy process.

#### 2.4. Objective, questions, hypotheses (if applicable).

The effectiveness study aims to clarify the extent to which positive psychotherapy compared to cognitive behavioral therapy and a control group (online positive psychotherapy with minimal therapeutic support - hereafter referred to as "minimally supported online PPT") in patients with generalized anxiety disorder, social anxiety disorder/social phobia and/or panic disorder with or without agoraphobia (hereinafter referred to for brevity as "anxiety patients") can reduce anxiety symptoms and increase overall life satisfaction, quality of life, and happiness. Through this study, the effectiveness of Positive Psychotherapy in the treatment of anxiety disorders will be evaluated for the first time in an online format.

Research hypotheses:

- 1) The anxiety patients\* who participated in the Positive Psychotherapy treatment program showed a significant decrease in anxiety symptomatology between pre- and postmeasurement.
- 2) Anxiety patients who participated in the Positive Psychotherapy treatment program showed a significantly greater decrease in anxiety symptoms compared to patients who participated in the minimally supervised online PPT treatment program.
- 3) The anxiety patients\* who participated in the Cognitive Behavioral Therapy treatment program showed a significant decrease in anxiety symptomatology between pre- and postmeasurement.

- 4) Anxiety patients who participated in the Cognitive Behavioral Therapy treatment program showed a significantly greater reduction in anxiety symptoms compared to patients who participated in the minimally supervised online PPT treatment program.
- 5) The anxiety patients who participated in the Positive Psychotherapy treatment program showed a comparable decrease in anxiety symptoms as the patients who participated in the Cognitive Behavioral Therapy treatment program.
- 6) Anxiety patients who participated in the Positive Psychotherapy treatment program experience a significant increase in happiness between pre- and postmeasurement through direct influence on positive emotions, on recognizing and using one's strengths, and on experiencing meaning.
- 7) The anxiety patients\* who participated in the Positive Psychotherapy treatment program experience a significantly greater increase in happiness experience through direct influence on positive emotions, on recognizing and using one's strengths, and on experiencing meaning compared to the patients\* who participated in the minimally supervised on line PPT.
- 8) The anxiety patients who participated in the Positive Psychotherapy treatment program experience a significantly greater increase in happiness experience compared to the patients who participated in the Cognitive Behavioral Therapy treatment program through direct influence on positive emotions, on recognizing and using one's strengths, and on experiencing meaning.
- 9) Anxiety patients who participated in the Positive Psychotherapy treatment program experience a significant increase in life satisfaction and quality of life between pre- and postmeasurement by directly influencing positive emotions, recognizing and using their strengths, and experiencing meaning.
- 10) Anxiety patients who participated in the Positive Psychotherapy treatment program experience a significantly greater increase in life satisfaction and quality of life than patients who participated in the minimally supervised online PPT treatment program by directly influencing positive emotions, recognizing and using one's strengths, and experiencing meaning.
- 11) Anxiety patients who participated in the Positive Psychotherapy treatment program experience a significantly greater increase in life satisfaction and quality of life than patients who participated in the Cognitive Behavioral Therapy treatment program by directly influencing positive emotions and self-compassion, recognizing and using one's strengths, and experiencing meaning.

- 12) The significant decrease in anxiety symptoms in the patients who participated in the Positive Psychotherapy treatment program remains stable over a period of three months.
- 13) The significant decrease in anxiety symptoms in patients who participated in the Cognitive Behavioral Therapy treatment program remains stable over a period of three months.
- 14) The significant increase in happiness among patients who participated in the Positive Psychotherapy treatment program remained stable over a period of three months.
- 15) The significant increase in life satisfaction and quality of life among patients who participated in the Positive Psychotherapy treatment program remained stable over a period of three months.
- 16) In terms of an exploratory question, it is assumed that the effects of Online Positive Psychotherapy with minimal therapeutic supervision will not remain stable over three months.

The process study will evaluate the process of therapy in Positive Psychotherapy and Cognitive Behavioral Therapy. In the process study, both the intra-session processes and the inter-session processes of therapy with Positive Psychotherapy and Cognitive Behavioral Therapy are to be evaluated. Furthermore, it will be determined which process variables (intra-session or inter-session processes) predict the success of therapy and to what extent Positive Psychotherapy and Cognitive Behavioral Therapy differ in the therapy processes. The intra-session processes will be assessed with the help of the hourly patient assessment form (STU-P). The participants will fill out this questionnaire in digital form after each session. Intersession processes are to be recorded with the help of the Intersession Questionnaire (ISF). The participants fill out this questionnaire in digital form before each session. The aim is to examine and evaluate the process. In this way, it may be possible to make changes to the manuals even after the end of the study and to gain insights into the therapeutic processes. The aim is to identify therapeutic process variables and thus optimize the therapy process.

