3.3. Characterization of participants

Minimum age: 18 Maximum age : 65

not personally capable of giving consent includable?

Yes No

Includable are

male and/or

female participants

3.4. Description of recruitment process (include all materials intended for use, e.g., advertisements):

Newspaper advertisements (have not yet been created), advertisements in online forums, internal university mailings, contacts to psychiatrists and psychotherapists, contacts to self-help groups, Facebook groups, Psychologie heute (Psychology Today).

3.5. Briefly describe the selection of participants and inclusion/exclusion criteria (sampling method, rationale, caseload estimate) (explicit rationale for inclusion of persons from protected groups, e.g., minors, temporarily or permanently incapacitated persons; if applicable).

Sample size as presented above, calculated using power analysis (G\*Power) criteria;  $p < .05$ ; 1-beta = .80; ES (between):  $d = 0.15 - 0.30$ ; 3 groups, 3 MZP. Required N=165 subjects, 55 per group.

Sample extraction: ad hoc/general sample; no other drawing is possible in this context.

Inclusion of protected groups not provided.

Inclusion criteria:

-age: 18 to 65

-Diagnosis of one of the following anxiety disorders: F40.1: Social anxiety disorder/social phobia; F41.0 Panic disorder with or without agoraphobia, F41.1 Generalized anxiety disorder.

-sufficient knowledge of German

-Average intellectual capacity (assessment during telephonic/video screening).

-Sufficient time for the weekly sessions and homework assignments.

-Acceptance of the study protocol

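### H5 claims that PPT is comparable to CBT without a margin, in a trial sized to detect a difference; 55 per arm could not show comparability within the range the protocol plans for

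*Protocol*

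**What the plan says.** Section 2.4 of the Protocol lists 16 efficacy hypotheses. Most predict a significant change or a significantly greater change than another arm. H5 differs: PPT patients "showed a comparable decrease in anxiety symptoms as the patients who participated in the Cognitive Behavioral Therapy treatment program". H12 and H13 state that the anxiety decrease under PPT and under CBT "remains stable over a period of three months". H14 and H15 say that the PPT gains in happiness and in life satisfaction and quality of life "remained stable over a period of three months". H16, labelled exploratory, concerns the third arm alone: "it is assumed that the effects of Online Positive Psychotherapy with minimal therapeutic supervision will not remain stable over three months".

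The sample size in item 3.5 rests on p<.05, power .80 and a between-group effect of d from 0.15 to 0.30, ending in "3 groups, 3 MZP. Required N=165 subjects, 55 per group". Section 2.11 plans intention-to-treat hierarchical mixed linear models of the changes from T1 to T2 and T3. The protocol contains no margin, tolerance, equivalence or non-inferiority test, or confidence-interval rule.

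**The concern.** A claim of similarity needs a stated size of difference that would still count as similar. That size also drives the sample size, so it is a design choice and not only an analysis detail that can wait for an SAP. Here N is fixed without it, using inputs for detecting a difference.

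The only standard visible in the neighbouring hypotheses is significance. Carried over to H5, it would turn p>.05 into support for comparability, and a smaller or more depleted trial would pass more easily. Comparing PPT with CBT is the stated purpose of the project (section 2.1), and item 3.19 calls CBT the treatment of choice for anxiety disorders. A conclusion that PPT does as well would therefore carry weight. H12-H15 raise the same issue in a weaker form, because nothing says how much loss between T2 and T3 is compatible with stability.

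**Working it through.** **Inputs.** From item 3.5: 55 per arm, p<.05, power .80, d from 0.15 to 0.30. Assumed: two-sided 5% test, outcome SD of 1, no clustering, no dropout unless stated. Baseline adjustment with correlation r multiplies the variance by 1-r²; r=.5 gives 0.75.

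**1. The plan's own figure.** The inputs do not fix one N, because the effect is a range and neither the test nor the correlation between time points is named. One route to 165 is the between-group factor of a repeated-measures ANOVA with f=0.20, m=3 and ρ=.5: λ = f²·N·m/(1+(m-1)ρ) = 0.04×165×3/2 = 9.9, power 0.804. The within-subject main effect at f=0.10, ρ=.5 also needs 165. Neither choice is stated. Both are tests for a difference.

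**2. H5 if non-significance were the criterion.** The noncentrality is d·√(n/2)/√(1-r²), with 2n-2 degrees of freedom. Probability of p≥.05:

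| True PPT-CBT difference | 55/arm, unadjusted | 55/arm, r=.5 | 55/arm, r=.7 | 44/arm, unadjusted |
|---|---|---|---|---|
| 0.15 SD | 88% | 85% | 81% | 89% |
| 0.30 SD | 66% | 56% | 41% | 72% |
| 0.40 SD | 45% | 33% | 17% | 54% |
| 0.50 SD | 26% | 15% | 5% | 36% |

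The 44 per arm column assumes 20% loss. Unadjusted at 55 per arm, the rate falls below 50% above d of about 0.38, and 80% power is reached only at d of 0.54.

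**3. What 55 per arm can show at true equality.** SE = √(2/55) = 0.191 unadjusted, and √(0.75×2/55) = 0.165 with r=.5. The 90% interval half-widths are 0.316 and 0.274 SD. Two one-sided tests (TOST) at 5% have power max(0, 2Φ(M/SE-1.645)-1). Non-inferiority at one-sided 2.5% has power Φ(M/SE-1.96).

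- M=0.30: M/SE = 1.573 and 1.817. TOST power 0% and 14%; non-inferiority power 35% and 44%.
- M=0.15: TOST power 0% both ways; non-inferiority power 12% unadjusted.
- M=0.50: TOST power 67% and 83%. This margin is wider than the effect range the protocol plans for.

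Unadjusted, 80% power for M=0.30 needs 175 per arm (non-inferiority) or 191 (TOST).

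**4. H12-H15 if a paired T2-T3 test were used.** With n=55 and noncentrality d·√n/√(2(1-ρ)), a true loss of 0.20 SD is non-significant with probability 0.692 (ρ=.5) or 0.532 (ρ=.7). At 0.30 SD the figures are 0.411 and 0.195. The correlations are assumptions.

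**The case against.** A reader might infer that the plan allows H5 and H12-H15 to be confirmed only by non-significance, and that it would wrongly confirm them most of the time. The document supports neither.

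- **No decision rule is stated.** Nothing says that p>.05 counts as support. An interval from the planned mixed model could be judged against a margin set in advance. The rates in step 2 are therefore conditional.
- **Most of the time does not hold throughout.** For H5 it fails above d of about 0.38, and at 0.30 SD with r=.7 (41%). For stability at a 0.30 SD loss the rate is about 20-41%. If the stated d were really Cohen's f, the differences would be larger and the rates lower.
- **Wrongly needs a threshold.** The protocol gives none. The figures matter if 0.15-0.30 SD matters, which is the range it planned for.
- **H12-H15 have another reading.** Given section 2.11, they can be read as a T1-T3 change that is still significant. That is an ordinary difference test, which low power makes harder to pass.
- **H16 is an exploratory, one-arm question.** It is tempting to say that the plan compares significance labels between arms, but no such comparison is stated. The three-by-three design and mixed model can supply the proper contrast, and the choice of contrasts is commonly left to an SAP.

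All of this stands. It narrows the point but leaves H5 without a margin, and leaves N chosen for a different question.

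**Conclusion.** The point holds for H5 in conditional form. The protocol predicts comparability, gives no margin, and sizes the trial for a difference. If a non-significant PPT-CBT result were taken as support, H5 would be accepted in about 66-88% of trials at true differences of 0.30 to 0.15 SD (56-85% with r=.5). A proper equivalence test within 0.30 SD would have 0-14% power at true equality, and non-inferiority 35-44%. These figures assume a two-sided 5% difference test (TOST at 5%, non-inferiority at one-sided 2.5%), 55 analysed per arm and no clustering. Dropout raises the acceptance rates, and so would clustering in therapy groups of six to eight (section 2.3).

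For H12-H15 the point is smaller: stable is undefined, and a non-significant T2-T3 test should not be made to define it. For H16 there is only advice on which contrast to use if arms are compared.

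**What to change.** 1. Restate H5 as the estimated PPT-CBT difference in anxiety change on one named scale, with its confidence interval. State that a non-significant difference will not be taken as comparability.
2. Use the word comparable only if the interval lies inside a margin fixed and justified before data are seen. Acknowledge that 55 per arm cannot be relied on to show equivalence within 0.15-0.30 SD. A margin of 0.5 SD chosen because the sample size nearly allows it would exceed the planned effect and would need its own justification.
3. For H12-H15, report the T2-T3 change with a confidence interval, and do not infer stability from a non-significant T2-T3 test. Set any tolerance separately for each outcome: these are within-arm changes on different scales, so the H5 margin does not carry over.
4. If the minimal arm's durability (H16) is compared with the other arms, use the arm by (T2-T3) contrast from the planned mixed model.

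The cost is rewording and one interval-based rule, with no new data unless a chosen margin calls for more participants. The trial may lose a comparability conclusion that its size could not support.

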#### Research hypotheses:

- 1) Anxiety patients whose intersession activity is emotionally positive show a greater decrease in their anxiety symptoms than patients whose intersession activity is negative. There is a significant correlation between the emotional occupation of the intersession processes and the decrease in anxiety symptoms.
- 2) Anxiety patients whose intersession activity is emotionally positive show a stronger increase in their happiness experience than patients whose intersession activity is negative. There is a significant correlation between the emotional occupation of the intersession processes and the increase in happiness.

- 3) Anxiety patients whose intersession activity is emotionally positive show a greater increase in their life satisfaction and quality of life than patients whose intersession activity is negative. There is a significant correlation between the emotional involvement of the intersession processes and the increase in life satisfaction and quality of life.
- 4) Anxiety patients whose intra-session activity has positive emotional connotations show a greater decrease in their anxiety symptoms than patients whose intra-session activity has negative connotations. There is a significant correlation between the emotional content of the intra-session processes and the decrease in anxiety symptoms.
- 5) Anxiety patients whose intra-session activity is emotionally positive show a stronger increase in happiness than patients whose intra-session activity is negative. There is a significant correlation between the emotional content of the intra-session processes and the increase in happiness.
- 6) Anxiety patients whose intra-session activity is emotionally positive show a higher increase in their life satisfaction and quality of life than patients whose intra-session activity is negative. There is a significant correlation between the emotional occupation of the intra-session processes and the increase in life satisfaction and quality of life.
- 7) Anxiety patients who show a higher level of intersession activity show a greater decrease in their anxiety symptoms at the end of therapy than those who show a lower level of intersession activity. There is a significant positive correlation between the intensity and frequency of intersession activities and the decrease in anxiety symptoms.
- 8) Anxiety patients who exhibit a higher level of intersession activity show a greater increase in their happiness at the end of therapy than those who exhibit less intersession activity. There is a significant positive correlation between the intensity and frequency of intersession processes and the increase in happiness.
- 9) Anxiety patients who exhibit a higher level of intersession activity show a greater increase in their life satisfaction and quality of life at the end of therapy than those who exhibit less intersession activity. There is a significant positive correlation between the intensity and frequency of intersession processes and the increase in life satisfaction and quality of life.
- 10) Anxiety patients who show a higher level of intra-session activity show a greater decrease in anxiety symptoms at the end of therapy than those who show less intra-session activity. There is a significant positive correlation between the intensity and frequency of intra-session processes and the decrease in anxiety symptoms.
- 11) Anxiety patients who exhibit higher levels of intra-session activity show a greater increase in happiness experience at the end of therapy.

bens, than those who have less intra- session activities. There is a significant positive correlation between the intensity and frequency of intra-session processes and the increase in happiness experience.

12) Anxiety patients who exhibit a higher level of intra-session activity show a greater increase in life satisfaction and quality of life at the end of therapy than those who exhibit less intra-session activity. There is a significant positive correlation between the intensity and frequency of intra-session processes and the increase in life satisfaction and quality of life.

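### Process hypotheses 1–12 are worded as correlations with change across both therapies together and name neither therapy nor baseline; restate them as an adjusted prediction model

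*Protocol*

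**What the plan says.** Section 2.4 of the protocol lists twelve process hypotheses. Each ends by naming a correlation between a process indicator and a decrease or increase in an outcome. Hypothesis 1 reads: "There is a significant correlation between the emotional occupation of the intersession processes and the decrease in anxiety symptoms". Hypothesis 10 reads: "There is a significant positive correlation between the intensity and frequency of intra-session processes and the decrease in anxiety symptoms". They are written for anxiety patients as a whole, as in "Anxiety patients whose intersession activity is emotionally positive show a greater decrease in their anxiety symptoms than patients whose intersession activity is negative". Section 2.3 limits the process study to PPT and CBT: "The control group is not included in the process study".

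Two other statements bear on these hypotheses. Sections 2.3 and 2.4 pose as a separate question "to what extent Positive Psychotherapy and Cognitive Behavioral Therapy differ in the therapy processes". Section 2.4 also promises a prediction answer: "it will be determined which process variables (intra-session or inter-session processes) predict the success of therapy".

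On the outcomes, efficacy hypothesis 8 says that PPT patients "experience a significantly greater increase in happiness experience compared to the patients who participated in the Cognitive Behavioral Therapy treatment program", and efficacy hypothesis 11 says the same for life satisfaction and quality of life. Efficacy hypothesis 5, by contrast, expects a similar fall in anxiety under both therapies.

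The one analysis statement, section 2.11, plans hierarchical mixed linear models under ITT for changes from T1 to T2 and T3. It neither lists nor excludes covariates and does not mention the process data.

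**The concern.** The hypotheses name a statistic that does not match the question the process study sets itself. A correlation with change across two therapies has two possible sources besides the process.

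**Therapy.** If PPT and CBT differ both in the process indicator and in the gain on an outcome, patients from the two arms form two shifted clouds. The pooled correlation is then non-zero even when there is none within either therapy. By the protocol's own expectations this can reach the hypotheses on happiness (2, 5, 8, 11) and on life satisfaction and quality of life (3, 6, 9, 12).

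**Baseline.** A change score contains the T1 score. If the process indicator is related to T1, it can correlate with change without any process effect, or a real association can be masked. This applies to all twelve.

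At stake is how the process results are read. Section 2.4 aims to identify process variables, and says the manuals might be changed in the light of them.

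**Working it through.** The protocol gives no sample size, power or error rate for the process hypotheses, so there is no stated figure to reproduce. The check asks how often a pooled correlation with change is significant when there is no process effect.

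**Inputs from the protocol**
- 55 per group (section 3.5), two therapies, so n = 2 × 55 = 110 before dropout.
- Alpha 0.05 (section 3.5). Sidedness is not stated; two-sided is assumed.
- Between-group d = 0.15 to 0.30 (section 3.5), taken as labelled.

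**Inputs that are assumptions**
- Difference between therapies in the process indicator: 0.5 to 0.8 SD.
- Correlation of the indicator with T1: 0.1 to 0.3 in size.
- T1–T2 correlation: 0.5, varied from 0.3 to 0.7.

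**Rejection rate for an induced correlation r** (Fisher z): Φ(−1.96 + z) + Φ(−1.96 − z), with z = atanh(r) × √107.

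**Step 1, therapy alone.** With equal arms that differ by dx in process and dy in change (in within-arm SDs), and no correlation within arms:

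r = (dx·dy/4) / √[(1 + dx²/4)(1 + dy²/4)]

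| dx | dy | r | rejection |
|---|---|---|---|
| 0.5 | 0 | 0 | 5.0% |
| 0.5 | 0.15 | 0.018 | 5.4% |
| 0.5 | 0.30 | 0.0375/1.042 = 0.036 | 6.6% |
| 0.8 | 0.15 | 0.028 | 6.0% |
| 0.8 | 0.30 | 0.06/1.089 = 0.055 | 8.8% |

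Simulation agrees. With dy = 0.30, 4,000 data sets per case gave 6.0% (dx = 0.5) and 9.4% (dx = 0.8); 20,000 gave 6.6% and 8.7%. With therapy in the model the rate is about 5%. The dy = 0 row is what the protocol expects for anxiety (efficacy hypothesis 5), so this route adds nothing to process hypotheses 1, 4, 7 and 10.

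**Step 2, baseline alone.** Suppose the indicator is related to T2 only through the observed T1 score. With equal SDs at T1 and T2:

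r = r(process, T1) × √[(1 − r(T1, T2))/2]

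With r(T1, T2) = 0.5, process–T1 correlations of 0.1, 0.2 and 0.3 give r = 0.05, 0.10 and 0.15, and rejection of 8%, 18% and 35%. Over T1–T2 correlations of 0.3 to 0.7 the range is 7% to 46%. A regression of T2 on indicator, T1 and therapy stays near 5%.

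The sign matters. At a process–T1 correlation of −0.3, two-sided rejection is about the same, but almost none of it lies in the hypothesised direction (0.03% in 20,000 simulated data sets). The bias then works against the hypothesis.

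**Step 3, when T1 adjustment misleads.** Suppose instead that the indicator follows true severity and that T1 and T2 are each true severity plus error. The indicator then correlates equally with T1 and T2, say 0.3 with each, with r(T1, T2) = 0.5. Its covariance with T1 − T2 is zero, so the change-score test holds 5%. The partial correlation with T2 given T1 is

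(0.3 − 0.3 × 0.5) / √[(1 − 0.09)(1 − 0.25)] = 0.15/0.826 = 0.18,

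and the T1-adjusted test rejects in about 47% (simulated: 47%). Neither model is safe in every case.

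**The case against.** A reader might infer that the protocol tests the hypotheses as raw, pooled, unadjusted correlations. It does not say so. The sentences stand under research hypotheses and state expected relationships. Section 2.11 names mixed models and rules out no covariate, and the question of what predicts success fits a regression at least as well. A statistical analysis plan, not at hand, may specify the model. This stands, and it limits the point to how the hypotheses are worded. It does not remove the point: the wording names a correlation in all twelve, section 2.11 does not cover the process data, and a later plan that adjusted would still have to depart from that wording.

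A reader might also infer that therapy confounds all twelve. It does not reach the four anxiety hypotheses, including the two quoted above, because efficacy hypothesis 5 expects comparable anxiety change. For the other eight, the protocol asks whether processes differ by therapy but does not predict that they do.

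Large false-positive rates from therapy differences are tempting too. They require outcome differences of 0.5 to 0.8 SD, above the protocol's own 0.15 to 0.30. The larger baseline figures depend on assumed correlations and on their sign.

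Finally, it might seem beyond debate that T1 adjustment is right. Step 3 of the working shows a plausible case in which it is the adjusted model that misleads.

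**Conclusion.** The concern holds in a limited form. The twelve hypotheses as worded do not separate the process association from therapy or baseline.

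- **Therapy:** for hypotheses 2, 3, 5, 6, 8, 9, 11 and 12, the false-positive rate rises from 5% to roughly 7% to 9% (below 10% in every simulation). This is at the top of the stated effect range and rests on assumed process differences of 0.5 to 0.8 SD. At d = 0.15 it is 5.4% to 6.0%. For hypotheses 1, 4, 7 and 10 the protocol's expectations imply no effect by this route.
- **Baseline:** all twelve are open to distortion, upward or downward. No single figure can be defended, because the protocol gives neither the process–baseline nor the T1–T2 correlation.

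The documents do not show that an unadjusted test is planned. The point is a worthwhile, nearly free correction to the wording. No treatment comparison rests on these correlations.

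**What to change.** Restate process hypotheses 1–12 in this form: the indicator predicts the outcome at T2 in a model with therapy arm and the T1 score of the same scale, with an indicator-by-therapy interaction to show whether the association is the same in PPT and CBT. State that the mixed model of section 2.11 applies to the process hypotheses. Report the therapy-adjusted change-score model as a sensitivity analysis, and where the two models disagree, say that the association depends on how baseline is handled.

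The cost is rewording and one extra analysis; therapy arm, T1 and T2 scores and process ratings are already collected. The revised text should also say that the associations remain non-causal, since adjustment for therapy and T1 does not deal with other common causes of process and outcome.
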